###### Short-Term Outcome Analyses

After 3 months, we will fit the aforementioned model to the data and compare the groups at T1 and T2 while adjusting for the covariates. The PROC GENMOD procedure in SAS (SAS Institute Inc) will be implemented to estimate the parameters of the model, where we specify a log-link function, Poisson distribution for the count data, an offset (which is a function of the total exposure), and the covariates. We will address overdispersion using negative binomial distribution. Overdispersion occurs when the expected count for the outcome variable is not the same as its variance. The generalized estimating equation procedure will be used to account for correlation induced by the repeated observations at T2.

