#### Sample Size Justification

Sample size determination was based on the primary outcome variable: number of drinking days in the past month across the repeated visits corresponding to T1, T2, T3, and T4 for the 3 groups (SAM only, SAM+TRAC, and SAM+TRAC-ER). Data on effect sizes from previous alcohol use interventions [34,35] and our preliminary data (within-participant correlation of 0.69) were used to derive the mean number of days of alcohol use and their SDs. With a final sample size of n=324 (after accounting for a 20% dropout rate with a total n=405), 108 (33%) participants in each group will give us at least 90% power at 5% type I error rate to detect a significant difference among the groups for an effect size of 0.071 when comparing the groups over the study period. This effect size is smaller than a *small* effect as defined by Cohen et al [36].

We expect our sample to have the following characteristics: 48.1% (195/405) cisgender men, 24.9% (101/405) transgender men, 20% (81/405) transgender women, and 6.9% (28/405) nonbinary individuals. Our sample will likely have a higher proportion of transgender participants compared to the general population due to recruitment within health clinics that provide care for transgender patients; we view this as a strength of our study, given the underrepresentation of gender minority individuals in previous alcohol intervention and HIV prevention research.

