#### Description of Study Arms

##### Overview

Participants will be enrolled in the study for 9 months, including the 2-month intervention period and multiple follow-up monitoring periods to assess long-term effects. All participants will begin with a 30-day monitoring period, which will establish baseline alcohol use through daily breathalyzer reading requests and surveys. After this 30-day period, they will complete additional baseline measures (T1) and then begin their assigned intervention, if applicable. After the interventions are delivered, participants will complete an additional self-report (T2). Subsequently, there will be 2 additional monitoring periods and assessments spread across the 9-month study period to assess long-term intervention effects, with some months involving no study activities. A depiction of the participation timeline is included in Figure 2, and details of study activities completed across the study timeline and RCT arms are provided in Table 1.

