##### Data Analysis Plan

###### Analysis of Alcohol Use Outcomes

Descriptive statistics for breathalyzer reading data will be summarized overall, by group (SAM only, SAM+TRAC, and SAM+TRAC-ER) and across time periods (T1-T4). The primary outcome is the number of drinking days in the past month, which is defined as the days on which individuals did not report 2 negative breathalyzer results. The rate of drinking (incidence of drinking) is the number of drinking days observed within the past month. The secondary outcomes include the number of drinks per drinking day, the number of days with binge drinking episodes, and the number of days for which HIV risk behaviors occur. All these outcomes are count data. The goal of this analysis is 2-fold: first, short-term analysis at the end of the 2-month intervention period, and, second, long-term analysis at the end of 9 months. We will fit a generalized linear model [50], with a general formulation for count data as follows:

g(E(y_i_)) = g(μ_i_) = x'_i_β (1)

where *y_i_* is the outcome variable for (*i*=1,2,3,...,*n*), *n* is the total number of observations, *μ*_i_=*E*(*y_i_*) is the expected count, *g* is the link function (a mathematical function connecting the counts with the explanatory variables), *β* is a vector of regression parameters to be estimated, and *x_i_* is a vector of independent covariates to be included in the model. These covariates include group, time, age (or age group), gender identity, sexual orientation, and site.

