###### Long-Term Outcome Analyses

At 9 months, the time variable will include observations at T1 to T4, and the procedure implemented for the short-term analysis will be repeated with the inclusion of additional covariates in the form of interaction terms among the groups and follow-up times (T1-T4). The interaction effect is central to the comparison of the groups over the study period. Generalized estimating equation fit criteria and quasi-likelihood under the independence model criterion value will be used to determine the adequacy of model fit. This modeling framework facilitates the easy computation of hypothesis tests and CIs for effects, which will form the basis of our inferential strategy in this project. Specifically, contrast statements will be used to test specific subgroup comparisons. Multiple imputation procedure will be implemented whenever necessary for missing data points. SAS (version 9.4 or higher) will be used for all analyses, and a standard 5% significance level will be used for all statistical tests.

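### The short-term model pools pre-intervention T1 with T2 under a single group effect and has no group-by-time term, so the end-of-intervention effect is biased toward the null

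*Protocol article*

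**What the plan says.** All references are to the protocol article.

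- **Outcome** (Analysis of Alcohol Use Outcomes): "The primary outcome is the number of drinking days in the past month".
- **Model terms** (same section): "These covariates include group, time, age (or age group), gender identity, sexual orientation, and site". No product of group and time is listed.
- **Short-term analysis** (Short-Term Outcome Analyses): "we will fit the aforementioned model to the data and compare the groups at T1 and T2 while adjusting for the covariates". For the fit, "we specify a log-link function, Poisson distribution for the count data, an offset (which is a function of the total exposure), and the covariates". A negative binomial distribution is the remedy for overdispersion, and generalized estimating equations (GEE) handle the correlation.
- **Long-term analysis** (Long-Term Outcome Analyses): the short-term procedure is "repeated with the inclusion of additional covariates in the form of interaction terms among the groups and follow-up times (T1-T4". The section then says: "The interaction effect is central to the comparison of the groups over the study period".
- **Timing of T1** (Description of Study Arms, Overview): after the 30-day monitoring run-in, "they will complete additional baseline measures (T1) and then begin their assigned intervention, if applicable".

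**The concern.** Read together, the three analysis sections define a short-term model with main effects only, in which T1 is an outcome occasion and not a baseline covariate. Such a model forces the same group ratio at T1 and at T2. Randomization makes the expected T1 ratio 1, because the intervention has not started. The one group coefficient is therefore a compromise between no difference at T1 and the real difference at T2. It does not estimate the intervention effect at the end of treatment.

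The end-of-intervention analysis is the first of the two goals named for the primary outcome, and it is scheduled separately after 3 months. Its rate ratio would lie too close to 1 and its test would lose power. The 9-month model could later give a visibly different T2 effect from the same T1 and T2 data.

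**Working it through.** **Inputs from the article.** The Sample Size Justification gives "within-participant correlation of 0.69", 108 per arm after dropout, a 5% type I error rate, an effect size of 0.071 and at least 90% power. It gives no mean, SD, rate ratio or T2 difference, so every effect size below except 0.071 is an assumption.

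**1. The article's own figures.**
- Recruitment: 324 / 0.80 = 405, as stated.
- Power, reading 0.071 as Cohen's f in a repeated-measures group-by-time test: λ = f²·N·m/(1−ρ) = 0.071² × 324 × 4 / 0.31 = 21.07, which gives 95.1% with four time points. With three time points λ = 15.81 and power is 90.6%. The stated figure of at least 90% reproduces.
- The same f tested as a group main effect over four time points: λ = 0.071² × 324 × 4 / (1 + 3 × 0.69) = 2.13, power about 24%. The stated power therefore matches an interaction test and not a pooled group effect.

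**2. Share of the effect retained, by hand.** In the balanced linear case with one record each at T1 and T2, the group coefficient is (0 + δ)/2, exactly 50% of the T2 effect δ. For a Poisson log-link model with independence working correlation and no other covariates, the group ratio equals the ratio of total counts. Assume a true T2 rate ratio of 0.70 and a control arm that is flat over time:
- One monthly count each at T1 and T2: (1 + 0.70)/2 = 0.85, and ln 0.85 / ln 0.70 = 0.163/0.357 = 46%.
- Two monthly T2 records, or one T2 record with two-month exposure: (1 + 1.40)/3 = 0.80, and ln 0.80 / ln 0.70 = 0.223/0.357 = 63%.

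**3. Share retained in simulated GEE fits.** Three arms were simulated with 3,240 per arm, an assumed baseline mean of 10 days, no true T1 difference and a true T2 rate ratio of 0.70. Poisson and negative binomial models were fitted with exchangeable and independence working correlation, on one large data set per setting. Shares are net of the chance T1 difference.

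| T2 layout | Share of T2 log rate ratio retained |
|---|---|
| One monthly count | 39%–49% |
| Two monthly records | 54%–66% |
| One record, two-month exposure | 52%–81% |

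In the one-count layout, the main-effects model returned a rate ratio of 0.86–0.89. With group-by-time added, the result was 0.69–0.71.

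**4. Power in the one-count layout** (normal approximation, unit SD, ρ = 0.69, n = 108 per arm, two-sided 5%).
- Main effect: z = (d/2)/√(2 × 0.845/108), where 0.845 = (1+ρ)/2.
- Interaction contrast: z = d/√(2 × 0.62/108), where 0.62 = 2(1−ρ).
- T2 adjusted for T1: z = d/√(2 × 0.524/108), where 0.524 = 1−ρ².

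The ratio of z values is (0.5/√0.845)/(1/√0.62) = 0.43 against the interaction contrast and 0.39 against baseline adjustment. Neither ratio depends on d. At d = 0.40 the three z values are 1.60, 3.73 and 4.06.

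| Assumed T2 difference (SD) | Main effect | Interaction | T2 adjusted for T1 |
|---|---|---|---|
| 0.20 | 12% | 46% | 53% |
| 0.30 | 22% | 80% | 86% |
| 0.40 | 36% | 96% | 98% |

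**5. Sensitivity of simulated power.** Two Poisson GEE simulations with a true T2 rate ratio of 0.80 gave different levels but the same direction. One (mean 10, 150 trials) gave 16% power for the main effect and 57% for the interaction, with mean coefficients of −0.087 and −0.204 against a true −0.223. The other (mean 12, SD 7, correlation 0.66, 300 trials) gave 23% and 84%, with rate ratios of 0.91 and 0.81.

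**The case against.** The article never says outright that the short-term test is the group coefficient pooled over T1 and T2. Its covariate list is not declared complete, comparing the groups at two named times could mean one comparison at each, and contrast statements are mentioned. An article also condenses a fuller plan. Part of this stands: the tested quantity is inferred. But the long-term section describes the interaction terms as additional to the short-term procedure, which removes most of the doubt. Without them the model cannot produce time-specific group contrasts.

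A reader might infer that the effect is halved, full stop. The documents do not fix that. The GEE sentence speaks of repeated observations at T2, the model has an exposure offset, and Table 2 has breathalyzer readings throughout the 8-week intervention. More than one T2 record, or a longer T2 exposure, is a live reading, and more of the effect then survives.

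A reader might also infer that a real short-term benefit would probably go unreported, or that the trial is underpowered. Neither follows. The 9-month model contains an undiluted T2-versus-T1 contrast, the sample size was set on T1 to T4, and its stated power reproduces as an interaction test. The dilution pulls toward no effect and does not create false positives.

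**Conclusion.** The point holds for the short-term analysis as written: its group effect is biased toward the null. About half of the T2 log rate ratio is retained with one equally weighted monthly count at each of T1 and T2, and roughly 40% to 80% across the T2 layouts that the text allows. The direction is the same in every layout examined. The test-statistic ratio of 0.43 rests on the one-count layout, the article's correlation of 0.69 and a normal approximation. The powers also rest on assumed T2 differences and are illustrations only. The 9-month analysis and the sample size calculation are not affected. What remains is an attenuated 3-month result on the primary outcome that could disagree with the T2 contrast from the later model. It should be corrected before the 3-month analysis is run.

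**What to change.** Add group-by-time to the short-term model, and prespecify the T2-versus-T1 contrast between each pair of arms as the short-term effect. Alternatively, model T2 drinking days alone with T1 drinking days as a covariate. Either removes the dilution, and in the one-count approximation baseline adjustment is slightly more powerful. State that the group main effect pooled over T1 and T2 will not be tested. In the same sentence, say how the 8 weeks of intervention data form the T2 record or records and the offset. If a fuller plan already contains the interaction, reconcile the article's text with it. The cost is one line of plan text and model code, with no extra data or participants.

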###### Long-Term Outcome Analyses

At 9 months, the time variable will include observations at T1 to T4, and the procedure implemented for the short-term analysis will be repeated with the inclusion of additional covariates in the form of interaction terms among the groups and follow-up times (T1-T4). The interaction effect is central to the comparison of the groups over the study period. Generalized estimating equation fit criteria and quasi-likelihood under the independence model criterion value will be used to determine the adequacy of model fit. This modeling framework facilitates the easy computation of hypothesis tests and CIs for effects, which will form the basis of our inferential strategy in this project. Specifically, contrast statements will be used to test specific subgroup comparisons. Multiple imputation procedure will be implemented whenever necessary for missing data points. SAS (version 9.4 or higher) will be used for all analyses, and a standard 5% significance level will be used for all statistical tests.

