### Objectives

The goal of the proposed study is to use this app to enhance TRAC by delivering messages that encourage participants to use strategies discussed during TRAC sessions when arriving at risky locations. When they leave these locations, they will complete a survey and a breathalyzer reading to collect event-level self-report and biological data on alcohol use and HIV risk. If their breathalyzer result indicates alcohol use, they will receive harm reduction messaging. It is expected that combining TRAC with EMI (Tracking and Reducing Alcohol Consumption and Environmental Risk [TRAC-ER]) will increase effectiveness by reinforcing topics discussed during sessions, providing in-the-moment messaging to address triggers, and collecting real-time alcohol use data.

We will conduct a randomized controlled trial (RCT) of the TRAC and TRAC-ER interventions, examining their effects on alcohol use and HIV risk behaviors among SMMT individuals compared with a SAM-only control group. We will examine 2 aims.

Aim 1: assess the effects of intervention conditions on drinking days (primary end point), drinks per drinking day, and binge drinking episodes (secondary end points).Hypothesis:TRAC and TRAC-ER will lead to significantly fewer drinking days compared with a SAM-only control group, with TRAC-ER having the strongest effects.Aim 2: assess the effects of intervention conditions on HIV risk behaviors (unprotected sex, number of partners, concurrent sex and substance use, and PrEP nonadherence).Hypothesis:TRAC and TRAC-ER will lead to significantly fewer HIV risk behaviors compared with a SAM-only control group, with TRAC-ER having the strongest effects.

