##### Data Collection Procedures

###### Overview

As this study is examining both short- and long-term effects and comparing them among the groups, the primary end point of the number of past-month drinking days will be assessed based on SAM results collected before T1, throughout the intervention, and before T3 and T4. Secondary end points include drinks per drinking day and binge drinking episodes. All other variables measured, including those related to HIV risk behaviors, will be used to conduct exploratory analyses. The sources of data for this RCT include SAM data (including surveys and breathalyzer results, discussed in detail previously), baseline and follow-up self-report measures (T1-T4), HIV and STI testing, app-based process measures, and qualitative interviews.

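### Every test is run at 5% over three arm pairs and two horizons with no primary horizon, contrast or gate; separately, HIV-risk days are secondary in one section and exploratory in another

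*Protocol article*

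**What the plan says.** All references are to the Protocol article.

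**Testing of the primary outcome**
- Long-Term Outcome Analyses sets one rule: "a standard 5% significance level will be used for all statistical tests".
- Objectives, Aim 1: "TRAC and TRAC-ER will lead to significantly fewer drinking days compared with a SAM-only control group, with TRAC-ER having the strongest effects". This covers TRAC against SAM only, TRAC-ER against SAM only, and TRAC-ER against TRAC.
- Analysis of Alcohol Use Outcomes gives the analysis two goals: "first, short-term analysis at the end of the 2-month intervention period, and, second, long-term analysis at the end of 9 months".
- The short-term analysis will "compare the groups at T1 and T2 while adjusting for the covariates". The long-term analysis adds group-by-time terms over T1 to T4 and states: "The interaction effect is central to the comparison of the groups over the study period".
- Sample Size Justification claims at least 90% power at a 5% type I error rate for one difference among the three groups, with effect size 0.071, a within-participant correlation of 0.69 and 324 completers.

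**Status of HIV-risk outcomes**
- Analysis of Alcohol Use Outcomes ends its list of secondary outcomes with "and the number of days for which HIV risk behaviors occur". The Abstract (Methods) and Study Design also group HIV risk behaviors with the primary and secondary outcomes.
- The Overview under Data Collection Procedures says: "All other variables measured, including those related to HIV risk behaviors, will be used to conduct exploratory analyses". Table 2 labels both the daily sexual-activity items and the T1 to T4 sexual-risk measure as exploratory.
- Aim 2 nevertheless carries a hypothesis of significantly fewer HIV risk behaviors in both active arms.

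**The concern.** These are two separate matters.

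First, the sample size budgets 5% for one question, while the analysis text allows 5% for each of several. An omnibus test cannot answer Aim 1, which needs arm-against-arm contrasts. Both horizons are analysed and neither is named as the one on which the primary claim rests. As written, nothing would stop a report from resting its main conclusion on whichever pair and horizon reached p<0.05.

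Second, the weight of a significant HIV-risk finding depends on which section is followed. Read one way it is a secondary result supporting a stated hypothesis; read the other way it only generates hypotheses. If this is not settled beforehand, it can be settled after the result is known.

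**Working it through.** **1. The plan's own figures.** 324/(1 − 0.20) = 405, as stated. Read 0.071 as Cohen's f (the metric is not named), with N = 324, m = 4 times and ρ = 0.69. For the group-by-time interaction in a repeated-measures ANOVA:

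λ = f²·N·m/(1 − ρ) = 0.005041 × 324 × 4 / 0.31 = 21.07, with 6 and 963 df.

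Power is 95.1%, so the claim of at least 90% holds. For the group main effect, λ = f²·N·m/[1 + (m − 1)ρ] = 6.533/3.07 = 2.13 with 2 and 321 df, and power is only 23.6%. Of these two, only the interaction test matches the stated power.

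**2. Number of tests.** 3 arm pairs × 2 horizons = 6 pairwise tests on the primary outcome. Sidedness is not stated; two-sided is assumed.

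**3. Correlation between horizons.** The document does not give it. For changes from T1 with equal within-person correlation ρ, the covariance of (T2 − T1) and (T4 − T1) is σ²(1 − ρ) and each variance is 2σ²(1 − ρ). The correlation is therefore 0.5 whatever ρ is, so the plan's 0.69 does not drive the result. The range 0 to 0.9 is shown.

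**4. Chance of at least one false positive.** Simulation with no true effect, three equal arms and normal test statistics:

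| What counts as success | Corr. 0 | 0.5 | 0.69 | 0.9 |
|---|---|---|---|---|
| Any of 6 pairwise tests, two-sided | 22.9% | 21.3% | 19.7% | 16.8% |
| Either active arm vs SAM, 2 horizons, two-sided | 17.3% | 16.2% | 15.1% | 12.6% |

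Other cases:
- Three pairs at one horizon: 12.2%.
- Six tests, with a 3-df interaction contrast per pair at 9 months instead of a T4-only change: 19.5%.
- Six tests, counting only the hypothesised direction, correlation 0.5: about 11.6%.
- One omnibus test per horizon: 8.2% with the 6-df interaction at 9 months. With a 2-df test at each horizon it is 9.2% at correlation 0.5, about 7% at 0.9, and 1 − 0.95² = 9.75% if the horizons are independent.
- The interaction over T1 to T4 as the only primary test: 5%.

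**5. HIV-risk status.** No arithmetic applies. The same outcome is secondary in Analysis of Alcohol Use Outcomes and exploratory in the Data Collection Overview and Table 2. Both labels cannot hold, and the exploratory one does not fit the confirmatory wording of Aim 2. The label does not enter any figure in step 4.

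**The case against.** A reader might infer that the plan carries a 21% false-positive risk on its primary claim. The document does not support that.

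- No section says that any one of six contrasts counts as success. The interaction is called central, and the stated power matches it. If it is the primary test, the error is 5% at 9 months.
- Aim 1 is worded conjunctively: both arms are to beat SAM only. With no effect, both do so at the same horizon in about 0.5% of trials at one horizon and 0.9% at either.
- The hypothesis is directional, so two-sided counts include results that nobody would present as success.
- Testing everything at 5% is not wrong in itself. An omnibus test followed by pairwise tests, all at 5%, is valid with three arms. What is absent is a gate, and gates are often left to a statistical analysis plan, which is not shown here.

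Much of this stands, and it makes 21% a conditional figure. It does not remove the point. The article calls the interaction central only in the long-term analysis; it does not make it the sole primary test or a gate. It gives the short-term analysis equal standing and the same 5%. Even the lenient reading of one omnibus test per horizon exceeds the single 5% in the sample size. The HIV-risk conflict lies in the text itself.

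**Conclusion.** Both points hold, and each should be corrected.

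**Multiplicity.** The article fixes 5% for all tests over two horizons and three implied pairs, and does not say which test carries the primary claim. The cost depends on the reading: 5% if only the T1 to T4 interaction counts, about 7% to 10% with one omnibus test per horizon, and about 17% to 23% if any of six ungated two-sided contrasts may count. These figures assume normal statistics, equal arms, no true effect and between-horizon correlations from 0 to 0.9.

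**HIV-risk status.** This is a plain contradiction between sections. It might be read as adding to the error on drinking days, but it does not. Its effect is confined to how an Aim 2 result may be interpreted.

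**What to change.** **Multiplicity.** In Long-Term Outcome Analyses, name the group-by-time interaction over T1 to T4 as the single primary test of drinking days at 5%. Only if it is significant, test the three arm pairs on the same group-by-time terms at 5% each. With three arms, if any two pairwise nulls are true then all three are, and the omnibus test covers that case. Family-wise error therefore stays at 5% without splitting alpha; Bonferroni over six tests would need 0.05/6 = 0.0083 each. Make the T2-only analysis a key secondary that cannot carry the primary claim alone.

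The cost is wording, with no added participants or data. The downside is that a pairwise claim needs the omnibus test to pass first.

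**HIV-risk days.** Before data are seen, give them one status in the Abstract, Objectives, Study Design, the Data Collection Overview, Table 2 and Analysis of Alcohol Use Outcomes. Either make them secondary throughout, or make them exploratory throughout and reword the Aim 2 hypothesis. This also costs wording only.
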